### Patient population

The study population will consist of 460 patients with NSTEMI enrolled at eight centers in Germany. Informed consent will be required prior to randomization.

Patients will be eligible for the study if they have: 1) ischemic symptoms such as angina pectoris for more than 20 minutes; 2) occurrence of previous symptoms less than 72 hours before randomization; 3) cardiac troponin levels above the 99th percentile; and 4) culprit lesion containing thrombus (TIMI thrombus grade 2 to 5 within the lesion) and intended early PCI.

Exclusion criteria will be presence of cardiogenic shock, STEMI, no identifiable culprit lesion, coronary morphology ineligible for thrombectomy (for example, very tortuous vessels or severe calcification), indication for acute bypass surgery, age less than 18 or more than 90 years, pregnancy, current participation in another clinical study, co-morbidity with limited life expectancy of less than 6 months or contraindications to CMR at study entry (for example, severe claustrophobia, implanted pacemakers or defibrillators, relevant metallic implants, known allergy to gadolinium, severe renal failure with creatinine clearance <30 ml/h), and contraindications for treatment with heparin, aspirin, or thienopyridines.

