### Cardiac magnetic resonance image acquisition

The primary endpoint (late MO) and secondary endpoints such as early MO, infarct size, and myocardial salvage will be assessed by CMR performed on a 1.5 or 3.0 Tesla scanner. Imaging will be performed on days 1 to 4 after randomization, using a standard scanning protocol (Figure 2). In brief, late MO and infarct size will be assessed in delayed enhancement short-axis images covering the whole ventricle acquired at mid-diastole approximately 15 minutes after bolus injection (0.2 mmol/kg bodyweight) of gadobutrol (Gadovist, Schering, Germany). An inversion recovery (IR) turbo gradient echo sequence will be used for image acquisition. The individual IR pre-pulse delay will be defined to obtain the maximal contrast between viable and necrotic myocardium. Early MO will be assessed 1 to 2 minutes after contrast-medium injection. For determination of edema/area at risk, short-axis slices covering the entire left ventricle (LV) before contrast administration will be obtained using a T2-weighted triple IR turbo spin-echo sequence. Assessment of LV function and volumes will be performed using a standard steady-state free precession technique, acquiring short-axis slices from base to apex and also horizontal and vertical long-axis views. Late and early MO, infarct size and area at risk will be expressed as percentages of the left ventricular mass (%LV), given by the sum of the mass of late and early MO regions, late enhancement and edema for all slices divided by the sum of the LV myocardial cross-sectional mass. The myocardial salvage index will be calculated as edema/area at risk minus infarct size divided by area at risk as described previously [24]. LVEF will be calculated from the short-axis functional views. The scan protocol and image analysis will be standardized at all sites and have been used effectively in previous studies [25-27]. All participating centers are experienced in using this type of conducted scan. CMR images will be sent to the CMR core laboratory at the University of Leipzig – Heart Center, Germany. The CMR core laboratory is highly experienced, has excellent reproducibility and low inter-observer and intra-observer variability for infarct size and myocardial salvage assessment, and has previously served as a core laboratory in studies of acute coronary syndromes [25-27]. Image analysis for the assessment of early and late MO, area at risk and infarct size, and total LV mass and volumes using a semi-automatic approach will be performed in anonymized form by blinded operators.

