### Study organization

The TATORT-NSTEMI Steering Committee is chaired by [name]. [name] (University of Leipzig – Heart Center, Leipzig, Germany), co-chaired by [name]. [name], (Institut für Herzinfarktforschung [IHF], Ludwigshafen, Germany), and [name]. [name] (University of Saarland, Campus Homburg/Saar, Homburg, Germany). The Steering Committee is responsible for the scientific content of the protocol and oversees the trial operations, and will perform the preparation of the primary manuscript and other publications arising from the TATORT-NSTEMI trial. Each participating center has a coordinator with extensive clinical-trial experience. All trial-related processes will follow the standard operating procedures of the IHF, which is an independent clinical-research organization providing biometry, study coordination, monitoring, and data management. Central monitoring will include a timely query-management process based on consistency and plausibility checks automatically generated from the database, combined with a dunning process for missing documentation and a reminder system in advance for upcoming visits. On-site monitoring will include initiation, regular visits, and close-out. During recruitment and follow-up, all centers will be visited regularly to check adherence to good clinical practice and trial protocol. The focus of the visits will be on the verification of informed-consent documents, eligibility criteria, key primary and secondary endpoints, and safety aspects.

The trial will be monitored by an independent DSMB. The CEC will adjudicate all clinical endpoints. The trial follows a standard study organization with a Steering Committee, DSMB, and CEC.

The study has been approved by the central ethical committee at the University of Leipzig and at all local ethics committees at the participating sites.

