## Trial status

Recruitment began in March 2011 and of December 2012, almost 360 patients had been enrolled. Given these inclusion rates, completion of enrollment is expected by July 2013. It is expected that complete data will be available in September 2013.

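### The renal exclusion limit is printed in ml/h instead of, almost certainly, ml/min, which makes it 60 times too low

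*Protocol article*

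**What the plan says.** The exclusion criteria under Patient population in the protocol article include a general item, "contraindications to CMR at study entry", followed by examples in brackets. One of these examples is "severe renal failure with creatinine clearance <30 ml/h". No other section of the article states a renal limit.

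Two other sections bear on it. Cardiac magnetic resonance image acquisition specifies a "bolus injection (0.2 mmol/kg bodyweight) of gadobutrol", so kidney function matters for every patient who is scanned. Study organization names among the aims of on-site visits the "verification of informed-consent documents, eligibility criteria, key primary and secondary endpoints, and safety aspects".

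**The concern.** A numeric limit in an exclusion criterion has to work as a screening rule. This one is meant to mark off severe renal failure, but 30 ml per hour lies far below any level that would define that category. A reader who applies the number as printed would pass almost everyone, including patients with a clearance of, say, 10 or 20 ml/min.

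At stake is whether the only stated renal limit before a contrast-enhanced scan can be used as written, by an investigator screening a patient or by a monitor checking eligibility. No calculation in the trial depends on it.

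**Working it through.** **Inputs**

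- Printed limit: 30 ml/h (Patient population).
- Presumed intended unit: ml/min. This is an inference from the words severe renal failure; the article does not state it.

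**The limit as printed**

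- Per minute: 30 ml/h ÷ 60 = 0.5 ml/min.
- Per day: 30 ml/h × 24 = 720 ml/day = 0.72 L/day.

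**The limit if ml/min was meant**

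- Per hour: 30 ml/min × 60 = 1800 ml/h.
- Per day: 30 ml/min × 1440 = 43,200 ml/day = 43.2 L/day.
- Ratio to the printed limit: 1800 ÷ 30 = 60.

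**What the printed limit leaves out**

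Clearances from 0.5 up to 30 ml/min are not flagged. As a share of the presumed interval from 0 to 30 ml/min this is (30 − 0.5) ÷ 30 = 98.3%. That is a share of the width of the interval, not of patients. The article does not say how many candidates would fall in this range.

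**Plausibility check with an assumed patient**

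Take a man aged 70 years who weighs 80 kg (values not in the article). By the Cockcroft-Gault formula, serum creatinine = (140 − age) × weight ÷ (72 × clearance).

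- Clearance 0.5 ml/min: 70 × 80 ÷ (72 × 0.5) = 5600 ÷ 36 = about 156 mg/dl, which is not physiologically possible.
- Clearance 30 ml/min: 5600 ÷ (72 × 30) = 5600 ÷ 2160 = about 2.6 mg/dl, which fits severe impairment.

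The conclusion does not rest on this illustration; the unit conversion is enough.

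**Link to the rest of the plan**

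The sample size comes from the difference in late microvascular obstruction, its standard deviation, the significance level and the power, with an allowance for failed thrombectomy and missing scans. The renal limit enters none of these.

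**The case against.** The strongest reply is that this is a misprint that no cardiologist would apply literally. The item is only an example under a broader exclusion, and the words beside the number already say what is meant. Either of these would exclude the relevant patients whatever unit is printed. This stands, and it is why the point is minor.

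A second reply is that the sites were not working from this text. Recruitment began in March 2011 and the article appeared in April 2013. Under Trial status it reports that by December 2012 "almost 360 patients had been enrolled", so about 460 − 360 = 100 of 460 (22%) remained to be enrolled at that date, and probably fewer at publication. The monitoring visits check adherence to the trial protocol, not to the article. This also stands: the article cannot show whether the full protocol or the case report form carries the same slip, and no wrong enrolment or contrast exposure can be inferred.

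Third, a clearance below 0.5 ml/min is still renal failure, so the number does not strictly contradict the words. That is correct. The fault is a limit set far too low to define the category.

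None of this makes the printed unit right. It is not a detail left to another document: the article states a value, and the value is wrong.

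**Conclusion.** The point holds, as a minor one. The printed limit equals 0.5 ml/min, and the presumed intended limit of 30 ml/min is 60 times higher. The conversion is certain. That ml/min was meant is an inference, but it is the only plausible reading. The error lies in the unit and not in the intent of the criterion. No effect on the patients enrolled, their safety or the trial's results has been shown or is claimed.

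**What to change.** Change the unit so that the criterion reads creatinine clearance <30 ml/min, after confirming the value against the full protocol. At the same time, confirm that the eligibility item in the electronic case report form uses ml/min. If the same slip is found in either place, correct it there as well.

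The cost is one unit changed in the text and one look at two existing documents. Design, sample size and analysis stay as they are.

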### Randomization and patient treatment

Patient randomization will be performed centrally, with a randomization ratio of 1:1 (n = 230 patients per group; see Figure 1 for study flow) using an internet-based randomization program. No stratification will be performed. All participating hospitals are high-volume tertiary care centers with experienced cardiologists performing all interventions. Manual thrombectomy will be performed in the thrombus aspiration group with an aspiration catheter commonly used in daily clinical routine (Eliminate^®^; Terumo Europe, Leuven, Belgium). In the standard PCI group, patients will be treated by conventional PCI in accordance with local practice without thrombectomy. Cross-over is not planned; however, if this occurs, the reasons will be recorded. Manual thrombectomy will be the only difference between the groups, and all other therapeutic procedures will be similar in both treatment arms.

**Figure 1 F1:**
[figure not shown]
**Study flow chart. **CMR, cardiac magnetic resonance; NSTEMI, non-ST-elevation myocardial infarction; PCI, percutaneous coronary intervention; TIMI, thrombolysis in myocardial infarction.

In vessels with a diameter of greater or equal than 2.5 mm, stent implantation is recommended. In both groups, the decision whether to use bare-metal or drug-eluting stents or whether to use glycoprotein IIb/IIIa inhibitors will be left to the discretion of the interventional cardiologist and the treatment decided upon will be recorded. Anticoagulant therapy including administration of heparin, bivalirudin, or low-molecular-weight heparin will be carried out in accordance with standard clinical practice and current guidelines. Additional treatment of other stenoses will be carried out if the interventional cardiologist deems it advisable, and will be recorded. Concomitant drug therapy for the treatment of NSTEMI will be administered based on the decision of the individual investigator and the common practice of the participating hospitals, in accordance with current guidelines. Anti-platelet therapy with initial loading dose will consist of aspirin 100 mg per day in combination with prasugrel 60 mg loading dose and subsequently 10 mg for 12 months for patients without contraindication to prasugrel. Patients pre-treated with clopidogrel should be switched to prasugrel whereas patients pre-treated with ticagrelor will not be switched. Post-infarction treatment includes administration of angiotensin-converting enzyme inhibitors or angiotensin-II-receptor antagonists, beta-blockers, and statins [11,12].

### Cardiac magnetic resonance image acquisition

The primary endpoint (late MO) and secondary endpoints such as early MO, infarct size, and myocardial salvage will be assessed by CMR performed on a 1.5 or 3.0 Tesla scanner. Imaging will be performed on days 1 to 4 after randomization, using a standard scanning protocol (Figure 2). In brief, late MO and infarct size will be assessed in delayed enhancement short-axis images covering the whole ventricle acquired at mid-diastole approximately 15 minutes after bolus injection (0.2 mmol/kg bodyweight) of gadobutrol (Gadovist, Schering, Germany). An inversion recovery (IR) turbo gradient echo sequence will be used for image acquisition. The individual IR pre-pulse delay will be defined to obtain the maximal contrast between viable and necrotic myocardium. Early MO will be assessed 1 to 2 minutes after contrast-medium injection. For determination of edema/area at risk, short-axis slices covering the entire left ventricle (LV) before contrast administration will be obtained using a T2-weighted triple IR turbo spin-echo sequence. Assessment of LV function and volumes will be performed using a standard steady-state free precession technique, acquiring short-axis slices from base to apex and also horizontal and vertical long-axis views. Late and early MO, infarct size and area at risk will be expressed as percentages of the left ventricular mass (%LV), given by the sum of the mass of late and early MO regions, late enhancement and edema for all slices divided by the sum of the LV myocardial cross-sectional mass. The myocardial salvage index will be calculated as edema/area at risk minus infarct size divided by area at risk as described previously [24]. LVEF will be calculated from the short-axis functional views. The scan protocol and image analysis will be standardized at all sites and have been used effectively in previous studies [25-27]. All participating centers are experienced in using this type of conducted scan. CMR images will be sent to the CMR core laboratory at the University of Leipzig – Heart Center, Germany. The CMR core laboratory is highly experienced, has excellent reproducibility and low inter-observer and intra-observer variability for infarct size and myocardial salvage assessment, and has previously served as a core laboratory in studies of acute coronary syndromes [25-27]. Image analysis for the assessment of early and late MO, area at risk and infarct size, and total LV mass and volumes using a semi-automatic approach will be performed in anonymized form by blinded operators.

**Figure 2 F2:**
[figure not shown]
**Cardiac magnetic resonance imaging scan protocol. **Flip, flip angle; IR, inversion recovery; SSFP, steady-state free precession; STIR, short tau inversion recovery; repetition time; TE, echo time.

### Assessment of secondary angiographic endpoints

Both before and after PCI, the culprit vessel should be visualized in several projections in order to obtain particularly precise display of the distal segments. Evaluation of thrombus burden will be performed before and after PCI, in accordance with the TIMI thrombus grade scale.

The flow within the infarct-related artery will be assessed using the TIMI criteria and the corresponding myocardial blush grades [28,29]. For the assessment of myocardial blush, it is especially important for the investigators to provide film material with a sufficiently long duration to allow evaluation of myocardial perfusion. A central blinded analysis for TIMI flow, blush grade, and thrombus burden will be performed at the angiographic core lab of the University of Saarland.

### Biomarker sub-study

In a single-center sub-study (University Leipzig – Heart Center, Germany) blood will be collected from the femoral sheath (peripheral blood) and from the infarct-related coronary artery for biomarker sub-studies for approximately 200 patients. In this technique, the plasma is separated by centrifugation at 3500 *g* for 10 minutes, and aliquots are stored at -80°C until used. Multiple biomarkers such as markers of CHF, inflammation, or myocardial-derived microRNAs (miRNAs) will be analyzed. In addition, assessment of platelet function will be performed.

### Thrombus composition sub-study

In a two-center study (University of Leipzig - Heart Center and University of Tübingen, both in Germany) that will include approximately 100 patients, the composition and key determinants of aspirated thrombi will be analyzed. This will include histological and immunohistological analysis, and analysis of specific biomarkers such as thrombus miRNAs. The probes will be stored at -80°C and transferred to the core facility at the University of Tübingen.

### Data and statistical analysis

The aim of the study is to demonstrate superiority of manual thrombus aspiration versus standard PCI without thrombus aspiration, based on the primary endpoint of late MO in the study patients.

At the time of planning the study, the only available data on MO in NSTEMI were from a study on a small number (n = 25) of patients [30]. Thus, we initially based our sample-size calculation on previous in-house studies of the University of Leipzig - Heart Center in patients with STEMI and NSTEMI. An absolute difference in the primary endpoint (late MO) of 1.0%LV between the two treatment groups was expected, and a standard deviation of 3.3%LV was assumed [17,26,27,31]. Based on α = 5%, a two-sided hypothesis test, and a statistical power of 80%, 172 patients per group would be needed to reject the null hypothesis of no difference between groups.

In the intervening time, two other studies on MO and NSTEMI were published, which reported a lower prevalence and extent of MO than expected [20,32]. Thus, the Steering Committee decided to perform a preliminary analysis on CMR parameters, including the first 60 patients enrolled in TATORT-NSTEMI. A prevalence of MO of approximately 40% with a median extent of 1.0%LV was oberserved. We thus decided to critically revise our sample-size calculation and adapt it based on the new available data and the preliminary analysis. We now expect an absolute difference in the primary endpoint (late MO) of 0.5%LV between the two treatment groups with a mean extent of 1.0%LV for late MO in the whole study cohort [20,32]. This difference is judged as clinically relevant [17,20,26,27,31]. A standard deviation of 1.8%LV is assumed [17,20,26,27,31,32]. Based on α = 5%, a two-sided hypothesis test, and a statistical power of 80%, 204 patients per group are needed to reject the null hypothesis of no difference between groups. On the basis of clinical experience and data in STEMI, it is further expected that it will not be possible to perform thrombectomy for 5% of all patients in the thrombectomy group, and that 10% of all patients, either will not undergo a CMR examination or their CMR images will be of insufficient quality for analysis [17,26,27]. This will result in a sample size of 2 × 230 randomized patients per group. We thus decided to include 60 additional patients after critical revision and adaptation of our initial sample-size calculation. This protocol modification was approved by the central ethics committee at the University of Leipzig. Sample-size calculation was performed using SigmaStat software (Version 3.5; Systat Software Inc., Chicago, IL, USA).

Pre-specified subgroup analyses by gender, presence of diabetes, TIMI thrombus burden (2 to 4 versus 5), TIMI flow pre-PCI (0 to 1 versus 2 to 3), and time from most recent symptoms to occurrence of PCI (<6 versus ≥6 hours), and additional administration of glycoprotein IIb/IIIa inhibitors will be performed.

All patients will be analyzed on an intention-to-treat basis. The differences in primary and secondary endpoints between the treatment groups will be assessed using an unpaired *t*-test. In addition, as a secondary analysis, the differences between the treatment groups in the main outcome will be assessed using an unpaired *t*-test adjusted by baseline values (ANCOVA). Categorical variables will be analyzed by Fisher’s exact test. The 95% confidence interval (CI) for differences in quantitative data will be displayed. For clinical events, relative risks and 95% CI will be reported. To identify factors associated with the observed results, univariate and multivariate regression analysis will be performed. To assess clinical outcome, Kaplan-Meier curves with log-rank comparison and Cox regression analyses will be performed. A two-tailed *P*-value of <0.05 will be considered significant.

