## Methods/design

The TATORT-NSTEMI trial is a prospective, multicenter, randomized, controlled, open-label study to compare PCI plus routine thrombus aspiration with PCI without thrombus aspiration in patients with NSTEMI and relevant thrombus burden who are undergoing early invasive reperfusion therapy. The study will determine if adjunctive thrombectomy is superior than PCI alone with respect to the extent of no-reflow/MO assessed by CMR in patients with NSTEMI.

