Previous data for patients with STEMI indicate that in approximately 10% of all patients the thrombus aspiration catheter fails to cross the lesion [37]. Because lesions in NSTEMI are often less complex and frequently display lower-grade stenoses, it can be expected that it will not be possible to perform thrombectomy in a smaller percentage (approximately 5%) of all patients in the thrombectomy group. To reduce the rate of unsuccessful thrombectomy, presence of a coronary morphology ineligible for thrombectomy (for example, patients with very tortuous vessels or severe calcification) will be a primary exclusion criterion. In addition, only interventional cardiologists experienced in manual thrombectomy will participate in this trial. Finally, blinding will not be possible as a result of the intervention used. However, several methods to restrict bias will be implemented, such as a central computerized randomization system; a blinded CEC to assess all relevant clinical events; a blinded CMR and angiographic core laboratory; and high standard requirements concerning the clinical level and experience of centers and investigators in terms of numbers of PCIs performed, cases of NSTEMI treated, and participation in cardiologic clinical trials.

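### The pre-specified subgroup by glycoprotein IIb/IIIa inhibitor use rests on a discretionary co-treatment that may follow and respond to the assigned procedure, so its arm comparisons are not protected by randomization

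*Protocol article*

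**What the plan says.** Protocol article, Data and statistical analysis: the pre-specified subgroups are gender, diabetes, TIMI thrombus grade (2 to 4 against 5), TIMI flow before PCI, time from symptoms to PCI, and finally "additional administration of glycoprotein IIb/IIIa inhibitors will be performed". No timing is attached to the last factor, and nothing sets it apart from the others.

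Randomization and patient treatment, in the text after Figure 1: for both groups, the decision "whether to use glycoprotein IIb/IIIa inhibitors will be left to the discretion of the interventional cardiologist", and the choice made is recorded. The same section says of the allocation that "No stratification will be performed".

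Methods/design calls the trial a "prospective, multicenter, randomized, controlled, open-label study", and the Discussion adds that "blinding will not be possible as a result of the intervention used". Patient population requires a "culprit lesion containing thrombus (TIMI thrombus grade 2 to 5 within the lesion) and intended early PCI", so a patient can be randomized only after angiography, with PCI still to come.

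One sentence points the other way (Randomization and patient treatment): "Manual thrombectomy will be the only difference between the groups, and all other therapeutic procedures will be similar in both treatment arms".

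**The concern.** The other five factors describe the patient, the vessel or the delay, and are settled by the time the intervention starts. Inhibitor use is the only one that is a treatment received. An operator who knows the arm and has seen the result of the assigned procedure may decide on it then. The article's own rationale makes dependence on the arm plausible. The Discussion says that aspiration lowers thrombus burden and distal embolization. It also cites an observational study in which thrombus scores of 4 or 5 fell from 40% to 7% of patients, and TIMI 3 flow rose from 36% to 66%, after aspiration. If aspiration changes the angiographic picture that much, it can also change which patients receive a discretionary antithrombotic drug.

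In that case users in the aspiration arm and users in the control arm are differently selected, and so are non-users. A difference produced by selection could then be reported as effect modification, with the same pre-specified standing as the baseline subgroups.

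**Working it through.** **1. Design inputs.** From Data and statistical analysis: difference 0.5 %LV, SD 1.8 %LV, two-sided α 5%, power 80%, 204 per group. Check: n = 2 × [1.8 × (1.960 + 0.842) / 0.5]² = 203.4, rounded up to 204. The stated figure reproduces and is not in dispute. It supplies the scale for what follows.

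**2. Source of the bias.** Let U be a procedural severity factor with mean 0 and SD 1, correlated r with late MO. Randomization balances U between the arms overall. With a true effect of zero, the expected difference (aspiration minus control) among users is

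r × 1.8 × [mean of U in aspiration users − mean of U in control users],

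and likewise among non-users. It is zero if use depends on U in the same way in both arms, and generally not otherwise. The overall difference stays at zero in every case.

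**3. Logistic scenarios.** None of these assumptions is in the document: r = 0.5, so r × 1.8 = 0.9; about 42% use in controls; log-odds of use = −0.4 + b × U + shift, with b = 1 and no shift in controls.

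| How use behaves after aspiration | Use, aspiration vs control | Users, %LV | Non-users, %LV |
|---|---|---|---|
| (a) same as control | 42% vs 42% | 0 | 0 |
| (b) less frequent (shift −0.7), b = 1 | 29% vs 42% | +0.11 | +0.10 |
| (c) less tied to severity (b = 0.3), no shift | 40% vs 42% | −0.27 | +0.21 |
| (d) unrelated to severity (b = 0), shift −0.7 | 25% vs 42% | −0.43 | +0.31 |

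Example, (d): mean U is 0 in aspiration users and 0.48 in control users, so the difference is 0.9 × (0 − 0.48) = −0.43. Scenario (c) shows that nearly equal rates of use do not rule out the artefact.

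**4. Threshold scenario.** Assume the drug goes to the worst 30% of controls and the worst 20% of aspirated patients by U, with r between 0.3 and 0.5. Mean U is 1.40 (top 20%) against 1.16 (top 30%), and −0.35 (bottom 80%) against −0.50 (bottom 70%).

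- Users: 0.24 × 0.3 × 1.8 = 0.13, up to 0.24 × 0.5 × 1.8 = 0.22 %LV.
- Non-users: 0.15 × 0.3 × 1.8 = 0.08, up to 0.15 × 0.5 × 1.8 = 0.13 %LV.
- Spurious interaction (users minus non-users): 0.05 to 0.09 %LV.

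**5. Against sampling error.** With 204 per arm and 30% and 20% use, the standard errors are:

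- users: 1.8 × √(1/61.2 + 1/40.8) = 0.36;
- non-users: 1.8 × √(1/142.8 + 1/163.2) = 0.21;
- interaction: √(0.36² + 0.21²) = 0.42.

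The threshold scenario shifts the subgroup estimates by about 0.4 to 0.6 standard errors, so the false-positive rate is roughly 6.5% to 10% instead of 5%. It shifts the interaction by only 0.1 to 0.2 standard errors (5.2% to 5.5%). Scenarios (c) and (d) imply larger interactions (−0.27 − 0.21 = −0.48 and −0.43 − 0.31 = −0.74 %LV), with the opposite sign among users.

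**The case against.** The article does not say when the inhibitor is given, or that it is given because thrombus or slow flow persists. It says only that use is discretionary and recorded. It also expects all other treatment to be similar in the two arms. For patients who started the drug before randomization, use is a legitimate baseline factor. All of this stands. A reader might infer that the comparisons within users and non-users simply are not randomized, or that the arms there are no longer comparable. The document does not support that flat statement, because bias arises only if use responds to the arm. However, the expectation of similar co-treatment does not make it so: the drug is left to an unblinded operator and use is not stratified. Scenario (c) shows that even similar rates would not suffice.

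A reader might also infer that the subgroup would make aspiration look harmful, or would show a sizeable false interaction. Neither follows. The threshold scenario gives an apparent excess of MO with aspiration but almost no interaction. Scenarios (c) and (d) give interaction but an apparent benefit among users. All of them also hold severity equal between the arms and the effect on MO at zero, which simplifies the suggested mechanism.

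Finally, this is one of six subgroup factors, no power or confirmatory claim is attached to it, and a condensed article may leave definitions and caveats to a fuller document. That limits the weight of the point but does not answer it. The article states the subgroup variable and calls it pre-specified, so this is a choice made and not a detail left out.

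**Conclusion.** The point holds in a limited form. As written, the factor is a co-treatment that may follow randomization and may respond to the assigned procedure, so randomization does not protect the arm comparisons within users or within non-users. If use does respond to the arm, spurious differences can arise with no true effect. Illustratively they run from 0 to about 0.4 %LV in either direction, against the 0.5 %LV on which the trial is sized. That range rests on assumed rates of use, an assumed link between use and severity, and an assumed correlation of severity with late MO. The document gives none of these, so neither size nor sign is established. The primary intention-to-treat comparison and the other five subgroups are unaffected.

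**What to change.** Remove inhibitor administration from the pre-specified subgroup list, and report its use by arm as a process outcome. If the subgroup is still wanted, either restrict it to use started before randomization, or keep it under an explicit label as an exploratory, non-randomized comparison.

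The cost is about one line of the analysis plan, and one listed subgroup is lost or downgraded. Use is already recorded, so reporting it by arm needs no new data. The restricted version needs start times relative to randomization, which the article does not say are recorded, and almost 360 of the 460 patients had been enrolled by December 2012. Use before randomization may also be too rare to analyse. Clinical use of the drug does not change under any option.
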